### Data Collection

#### Feasibility Outcomes

The primary feasibility outcomes are to estimate the proportion of women who were randomized out of those identified from the clinical registers (study population); the proportion of women who take up the intervention out of those in the intervention arm, to be defined by measures of digital analytics (data will be collected on date of log in, time spent on each component of the app, and total time spent on the app); and the proportion of women who are withdrawn or lost to follow-up out of those randomized (ie, those who provide no primary or secondary outcome data).

The secondary feasibility outcomes are to estimate the proportion of women identified from clinical registers (study population) who give consent for screening for eligibility; the proportion of women who were randomized out of those eligible to participate; the proportion of those who completed the secondary outcomes at follow-up out of those randomized; and the number of women randomized per month overall and per month per study site.

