### Randomization

Women who meet study inclusion criteria and consent to study participation will be randomized using simple block randomization to two groups. The randomization system will be set up online using the system Sealed Envelope [39]. The randomization list will be generated by clinical research unit (CRU) officers prior to the first participant’s baseline visit at 30 weeks of pregnancy, using random permuted blocks of 2 and 4 to treatment A or B in a ratio of 1:1 to ensure that the groups are balanced periodically. Once the randomization list has been generated, access to the list will be password protected. Only CRU officers will have access to the list and will be responsible for randomizing participants. At 30 weeks of pregnancy during the baseline visit, once the consent form has been signed, eligibility has been confirmed, and baseline assessments have been completed, a research member in the clinic will call CRU officers to obtain group allocation. The CRU officers will access the randomization list the same day to obtain the allocation. Recruitment and randomization will be ongoing until each arm of the study comprises 30 participants.

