#### Secondary Outcomes

##### Anthropometric

Anthropometric outcomes will be collected antenatally at 36 weeks gestation (time 1), and at 3 (time 2), 6 (time 3), 9 (time 4), and 12 (time 5) months post partum. They include weight (kg), height (cm; at time 1 only), BMI (kg/m2), and body fat percentage.

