##### Biomedical

Biomedical outcomes will be collected antenatally at 36 weeks gestation (time 1) and at 6 (time 3) and 12 (time 5) months post partum. They include systolic and diastolic blood pressure (mm Hg), total cholesterol (mmol/L), LDL cholesterol (mmol/L), HDL cholesterol (mmol/L), HbA_1c_ (mmol/mol), fasting plasma glucose (mmol/L), OGTT (mmol/L; time 3 and 5 only), and insulin resistance (HOMA-IR).

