#### Plans for Statistical Analysis

Data will be double entered into an SPSS (IBM Corp) data set, and data analysis for the study will be performed using SPSS. Statistical analysis and reporting will be presented in line with the CONSORT (Consolidated Standards of Reporting Trials) guidelines [50]. Statistical analyses will primarily be descriptive, aiming to provide estimates related to feasibility parameters and to help inform power calculations for a future definitive trial.

For the primary outcomes of feasibility, we will calculate proportions or rates and appropriate CIs. We will consider whether a larger phase III effectiveness trial is feasible based on three potential factors: ≥25% of eligible women agree to be randomized, ≥50% of women in the intervention arm take up the intervention, or there is less than <20% attrition (women withdrawn from the study or lost to follow-up).

The secondary outcomes will be summarized using appropriate summary statistics overall and by randomization arm at each outcome time point. Normally distributed continuous variables will be summarized using the mean and SD, skewed continuous variables using the median and IQR, and categorical variables using frequencies and proportions. As the majority of the secondary outcomes are continuous and repeatedly measured, we will estimate the mean difference between the arms using linear mixed effects models with a random intercept at the participant level. The repeatedly measured outcomes will be the dependent variables, with the independent variables being trial arm, time, and a trial arm by time interaction term to extract differences at different time points. We will use analysis of covariance models where possible (ie, also include the baseline measure of the outcome as another independent variable). Appropriate 95% CIs will be calculated for the overall group and by trial arm, but as this is a feasibility study, we will not compare these statistically nor provide a *P* value for comparisons between arms. We will also not impute missing data, although fitting the mixed effects models using maximum likelihood will help account for missing data under a missing at random assumption. Some variables (eg, PHQ-9 and conversion to T2D [HbA_1c_ of 48 mmol/mol]) will also be summarized (but not analyzed) as categorical variables based on their clinical cutoffs. Smoking status and the obstetric outcomes that will only be measured once will also be summarized rather than modeled.

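### The primary attrition outcome has no time point and counts only women who give no data, so a woman seen once at 36 weeks' gestation is retained; the <20% factor is worded differently

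*Protocol article*

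**What the plan says.** All references are to the protocol article.

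- **Feasibility Outcomes** lists, as the third primary feasibility outcome, the share of women withdrawn or "lost to follow-up out of those randomized (ie, those who provide no primary or secondary outcome data". No visit or time point is attached. Uptake of the intervention, measured by app log-ins and time on the app, is another primary outcome in the same list. Completion of the secondary outcomes at follow-up is a separate, secondary feasibility outcome, with neither a time point nor a threshold.
- **Randomization** puts allocation at the baseline visit: "At 30 weeks of pregnancy during the baseline visit".
- **Secondary Outcomes** then start early. For weight, BMI and body fat: "Anthropometric outcomes will be collected antenatally at 36 weeks gestation (time 1), and at 3 (time 2), 6 (time 3), 9 (time 4), and 12" months post partum. For blood pressure and blood tests: "Biomedical outcomes will be collected antenatally at 36 weeks gestation (time 1) and at 6 (time 3) and 12 (time 5) months post partum".
- **Plans for Statistical Analysis** gives three potential factors for judging whether a larger trial is feasible. One is that "there is less than <20% attrition (women withdrawn from the study or lost to follow-up". The reference to women giving no data is absent here, and again there is no time point.
- The **Introduction** and **Overall Aim** sections describe a 15-month trial that runs to 12 months post partum.

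**The concern.** The parenthesis in Feasibility Outcomes reads as a definition, and its operative word is *no* data. One weight or blood pressure reading at 36 weeks is secondary outcome data, so it takes a woman out of the numerator for good. Taken as written, the measure captures loss before the first of five outcome visits and is silent on the 12 postpartum months, where the future trial's outcomes lie.

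The word *primary* adds a second problem. App log-ins are primary outcome data, so a woman in the intervention arm who only opens the app could arguably count as retained without attending any visit. Controls have no such route, so the measure could differ between arms for reasons unrelated to retention.

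The analysis section can be read more broadly. A woman who formally withdraws at 6 months post partum counts there, but not under a strict reading of the primary outcome. The attrition figure is meant to inform whether and how to run a definitive trial, and two people applying the article could report different figures from the same data.

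**Working it through.** **The plan's own figures.** The article gives no calculation and no expected rate for attrition. Its only computed figure concerns another proportion, about 10% to within 8 points. Taking n = 60, 1.96 × √(0.10 × 0.90 / 60) = 0.076, which agrees with that statement but says nothing about attrition.

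**Inputs from the article.** 60 randomized, 30 per arm; randomization at 30 weeks; five outcome visits (36 weeks' gestation, then 3, 6, 9 and 12 months post partum); threshold <20%. Since 12/60 = 20% is not below 20%, the factor is met only with at most 11 of 60 counted as lost.

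**Assumptions.** True loss by 12 months, A, is varied because the article gives none. A woman who misses 36 weeks is taken not to return. App log-ins are ignored; counting them as data would lower the numerator further. Birth is taken at 40 weeks, so follow-up is 10 + 52 = 62 weeks, of which 36 − 30 = 6 precede the first outcome visit.

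**Formulas.** Let q be the chance that a woman is counted as lost.

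- 12-month definition: q = A.
- No-data definition, equal proportional loss before each of five visits: q = 1 − (1 − A)^(1/5).
- No-data definition, constant weekly loss: q = 1 − (1 − A)^(6/62).
- Chance of meeting the factor: P(X ≤ 11), with X binomial (60, q).

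For A = 40%, q is 1 − 0.6^(1/5) = 9.7% (about 5.8 women expected) or 1 − 0.6^(6/62) = 4.8% (about 2.9 women). The number actually lost by 12 months would be about 0.40 × 60 = 24.

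| Assumed 12-month loss A | P(met), 12-month definition | No-data definition, even across visits: q; P(met) | No-data definition, constant weekly: q; P(met) |
|---|---|---|---|
| 20% | 0.45 | 4.4%; 1.00 | 2.1%; 1.00 |
| 25% | 0.15 | 5.6%; >0.999 | 2.8%; 1.00 |
| 30% | 0.03 | 6.9%; 0.999 | 3.4%; 1.00 |
| 40% | 0.0003 | 9.7%; 0.988 | 4.8%; 1.00 |
| 50% | about 0 | 12.9%; 0.919 | 6.5%; >0.999 |

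Under the no-data definition, the chance of meeting the factor stays at or above 0.95 until 12-month loss reaches about 47% (even across visits) or 73% (constant weekly).

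**Sensitivity to timing.** If half of all loss falls before 36 weeks, q = A/2:

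| A | q | P(met), no-data definition |
|---|---|---|
| 30% | 15% | 0.82 |
| 40% | 20% | 0.45 |
| 50% | 25% | 0.15 |

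**The case against.** Five points can be made for the plan.

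1. *The factor does not carry the parenthesis.* On an ordinary reading of the analysis section, a woman seen at 36 weeks and never again is lost to follow-up and would count. This stands. The probabilities for the no-data definition apply only if the primary-outcome definition governs the factor, and the article does not say which does.
2. *The literal reading proves too much.* Recruitment is also a primary outcome, so strictly every randomized woman has contributed primary data and attrition could only be 0%. That cannot be intended. It points to loose wording rather than a deliberate choice, but it does not tell the reader what to count.
3. *Heavy loss would still be seen.* Completion of secondary outcomes is reported, summaries are planned by arm at each time point, reporting follows CONSORT, and missing data are examined. A reader might infer that postpartum loss would go unreported; the article does not support that. What remains is narrower: such loss may not enter the primary attrition figure or the <20% comparison, and the completion outcome has no time point or threshold with which to replace them.
4. *This is not a strict go/no-go rule.* The article speaks of potential factors to be considered and joins the three with *or*. That stands; meeting this factor does not by itself settle progression.
5. *The timing of loss is unknown.* A reader might infer that the factor is met almost automatically. That holds when loss is spread over follow-up, but not when it is concentrated before 36 weeks, as the 0.45 shows.

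Leaving detail to an analysis plan is no answer here, because the article fixes a definition.

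**Conclusion.** The point holds in this form: the primary attrition outcome is defined without a time point and in a way that counts a woman seen only at 36 weeks' gestation as retained, and the article states the <20% factor in different terms. Both defects follow from the text alone and do not depend on when loss occurs.

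The size of the consequence does depend on assumptions: that the no-data definition governs the factor, and how much loss there is and when. At an assumed 40% loss by 12 months, twice the threshold, the chance of meeting the factor runs from 0.45 (half the loss before 36 weeks) to 0.988 (even across visits) and about 1.00 (constant weekly), against 0.0003 on a 12-month definition. The unequal treatment of the arms through app log-ins is a possible reading of the word *primary*; its size cannot be computed from the article.

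**What to change.** Use one definition in both Feasibility Outcomes and Plans for Statistical Analysis: attrition is the number of randomized women with no outcome data of any kind at 12 months post partum (time 5), including those who withdrew earlier, divided by all women randomized. State that app analytics and recruitment data do not count as outcome data for this purpose. Apply the <20% factor to this quantity and report it by arm.

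Any time 5 measure should suffice. Requiring particular ones, such as weight or HbA1c, would label as lost a woman who gave only questionnaire or dietary data at 12 months.

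The change costs one definition and a matching edit in the second section. Time 5 assessments are already scheduled, so no new data are needed. The downside is that the reported attrition will be higher and the <20% factor harder to meet.

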#### Secondary Outcomes

##### Anthropometric

Anthropometric outcomes will be collected antenatally at 36 weeks gestation (time 1), and at 3 (time 2), 6 (time 3), 9 (time 4), and 12 (time 5) months post partum. They include weight (kg), height (cm; at time 1 only), BMI (kg/m2), and body fat percentage.

##### Biomedical

Biomedical outcomes will be collected antenatally at 36 weeks gestation (time 1) and at 6 (time 3) and 12 (time 5) months post partum. They include systolic and diastolic blood pressure (mm Hg), total cholesterol (mmol/L), LDL cholesterol (mmol/L), HDL cholesterol (mmol/L), HbA_1c_ (mmol/mol), fasting plasma glucose (mmol/L), OGTT (mmol/L; time 3 and 5 only), and insulin resistance (HOMA-IR).

##### Psychological

Psychological outcomes will be collected at 6 (time 3) and 12 (time 5) months post partum. They include self-efficacy (total SEE score), mother-infant relationship (total Maternal Postnatal Attachment Scale score), and depressive symptoms (total PHQ-9 score).

##### Lifestyle

Lifestyle outcomes will be collected at 6 (time 3) and 12 (time 5) months post partum. They include dietary intake (standardized multiple-pass 24-hour dietary recall), physical activity (total SF-IPAQ score), step count (mean steps, inbuilt smartphone function), and infant feeding practices (total score).

#### Process Evaluation Outcomes

A mixed methods six-component process evaluation framework will be used. Data collection methods for each component of the process evaluation are described below.

##### Recruitment

Participant recruitment flow; number of eligible, consented, screened, enrolled, and randomized; reason for nonparticipation or exclusionParticipant characteristics, sociodemographic dataRecruitment strategy, description of recruitment pathways into MY GODDESS

##### Dose delivered

Total number of MyManis app downloadsTotal number of group support sessions delivered

##### Dose received

Digital analytics of MyManis app including date of log in, total number of log ins per month, length of log in, time spent on each component of the appGroup support attendance logs

##### Program implementation/fidelity

IT logs of the MyManis app will be collated on technical issues reported when using the interventionAssessment of competency of MI-trained dieticians in delivering group support

##### Provider experience

Semistructured interviews with clinical research members who were responsible for participant recruitment and MI-trained dieticians who were delivering group support. Interviews will be conducted at the conclusion of the study and guided by an interview schedule.

##### Participant experience

Semistructed interviews to understand participant experiences of the trial, satisfaction, and acceptability (women in the intervention arm only). Data will also be collected on the acceptability of assessing the mother-infant relationship via observation from participants perspectives at 3 months. Mother-infant relationships will be assessed via video recording obtained either at the clinic or via videoconference at the woman’s home. The recordings will aim to include both the mother’s and baby’s faces to enable coders to adequately visualize subtle movements, facial expressions, and vocalizations. Mothers will be advised to “talk and play with your baby as you normally would” prior to the recording. Recordings will be uploaded to a password‐protected computer and assessed and coded based on the Child Adult Relationship Experimental Index [47].Satisfaction survey: a purpose-designed survey regarding acceptability and perceived usefulness of the MyManis app

#### Clinical Variables

The following maternal and neonatal variables will be collected to describe the sample and the potential attrition and generalizability of a larger trial in this population. These variables will be collected at 3 months post partum (time 2) from postnatal records by a research team member. While we will not statistically assess them as such in this feasibility study, these variables may also be potential predictors or modifiers of postpartum outcomes at the later time points, which we may need to consider for a larger trial. These include maternal medical data (gestational hypertension, gestational hypercholesterolemia, pre-eclampsia); maternal pregnancy and birth data (place of antenatal care, date of admission, date of delivery, place of delivery, date of discharge, delivery method, pregnancy complications, birth complications, or breastfeeding status on discharge); and neonatal data (birth weight; appearance, pulse, grimace, activity, and respiration [APGAR] score 5 minutes; congenital anomaly; congenital pneumonia/heart defects; admission to neonatal intensive care; special care or qualified on ward; length of stay).

### Statistical Analysis

#### Sample Size

The aim is to recruit 30 women per arm, as this should be a large enough sample to estimate parameters such as the SD, which in turn can be used to estimate the sample size for an appropriately powered full-scale RCT [48]. This sample should also allow us to estimate the 95% CI for the primary feasibility outcome of the proportion randomized of those eligible, which we estimate will be approximately 10%, to a CI of within +/-8% [49]. This was calculated as:

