**Methods:**

This is a two-arm parallel feasibility RCT. A total of 60 Malaysian women with GDM will be randomized in the antenatal period to receive the intervention or standard care until 12 months post partum. The intervention is a diabetes prevention intervention delivered via a smartphone app developed based on the Information-Motivation-Behavioral Skills model of behavior change and group support using motivational interviewing. The intervention provides women with tailored information and support to encourage weight loss through adapted dietary intake and physical activity. Women in the control arm will receive standard care. The Malaysian Ministry of Health’s Medical Research and Ethics Committee has approved the trial (NMRR-21-1667-60212).

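### The ±8-point precision quoted for the recruitment proportion fits a denominator of about 60, but 60 is the numerator; the design implies about ±2.4 points

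*Protocol article*

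**What the plan says.** The Sample Size section gives two reasons for the target. The first concerns variability: "The aim is to recruit 30 women per arm, as this should be a large enough sample to estimate parameters such as the SD". The second concerns precision: "This sample should also allow us to estimate the 95% CI for the primary feasibility outcome", which that section identifies as "the proportion randomized of those eligible, which we estimate will be approximately 10%, to a CI of within +/-8" percentage points. A formula is announced directly afterwards.

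Two other places fix what the 60 women are. The Methods paragraph of the abstract says "A total of 60 Malaysian women with GDM will be randomized in the antenatal period". The Randomization section says "Recruitment and randomization will be ongoing until each arm of the study comprises 30 participants". Neither the Sample Size section nor any other gives a planned number of eligible women.

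The Feasibility Outcomes section names a different primary recruitment proportion: "the proportion of women who were randomized out of those identified from the clinical registers (study population"). It lists "the proportion of women who were randomized out of those eligible to participate" among the secondary feasibility outcomes.

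**The concern.** The precision of a proportion depends on its denominator. The sentence credits the precision to the 60 women recruited, yet the trial stops when 60 women have been randomized. Those 60 are the successes being counted, not the women among whom they are counted. The denominator is the pool of eligible women, which at the assumed 10% is about ten times larger.

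As printed, three figures cannot all describe one design: 60 women randomized, 10% of eligible women randomized, and a half-width of about 8 points. What is at stake is one of the two stated reasons for the sample size, and a published precision figure that readers planning the definitive trial may take at face value.

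**Working it through.** **Inputs**
- Number randomized: 60, as 30 per arm (abstract, Randomization, Sample Size).
- Expected proportion randomized of those eligible: 0.10 (Sample Size).
- Confidence level: 95%, z = 1.96 (Sample Size).
- Stated half-width: within 8 points (Sample Size).

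**Step 1. Reproduce the stated figure.** The simple (Wald) half-width is z × √(p(1 − p)/n).
- n = 60: 1.96 × √(0.09/60) = 0.0759, or 7.6 points, which rounds to 8.
- n needed for exactly 8 points: 1.96² × 0.09 / 0.08² = 54.0.
- n = 30 (one arm): 1.96 × √(0.09/30) = 10.7 points.
- n = 600: 1.96 × √(0.09/600) = 2.4 points.

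Of these denominators, only one of about 54 to 60 gives the stated figure. The total sample of 60 is the natural candidate, because the sentence attributes the precision to the sample.

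**Step 2. Check that denominator against the design.** If 60 were the number of eligible women, 10% would give 0.10 × 60 = 6 randomized women. The design randomizes 60.

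**Step 3. Use the denominator that the design implies.** 60 / 0.10 = 600 eligible women.
- Wald half-width: 2.4 points.
- Wilson interval for 60/600: 7.8% to 12.7%.
- Clopper-Pearson interval for 60/600: 7.7% to 12.7%.

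**Step 4. Allow for the stopping rule.** Recruitment continues until 60 are randomized, so the number of eligible women is random and the number randomized is fixed. The approximate half-width under this inverse sampling is z × p × √((1 − p)/60) = 1.96 × 0.10 × √(0.9/60) = 2.4 points. The answer does not change.

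**Step 5. Vary the proportion.** The Plans for Statistical Analysis section uses a 25% threshold for the same proportion. At 25% the denominator would be 60 / 0.25 = 240 and the half-width 1.96 × √(0.1875/240) = 5.5 points. This is again not 8.

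**Step 6. Proportions whose denominators the sample does fix.** The thresholds come from Plans for Statistical Analysis.
- Attrition of 20% among 60 randomized: 1.96 × √(0.16/60) = 10.1 points (Wilson interval 11.8% to 31.8%).
- Uptake of 50% among 30 in the intervention arm: 1.96 × √(0.25/30) = 17.9 points (Wilson interval 33% to 67%).

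**The case against.** **The formula has not been seen.** It is missing from the text available, so the use of 60 is an inference. Any n from about 48 to 61 also rounds to 8 points. This stands as a limit on how the error arose, but not on the result: the sentence credits the precision to the sample, and 60 randomized at 10% gives 2.4 points whatever formula was printed.

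**The statement is literally met.** A half-width of 2.4 points is within 8. This also stands. A reader might infer that the trial falls short of its promised precision; the arithmetic shows the opposite, since the half-width is overstated and the precision understated.

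**Nothing in the trial depends on the figure.** The SD rationale comes first and is untouched. The Plans for Statistical Analysis section promises appropriate confidence intervals for the feasibility proportions, which can be calculated from the women actually counted. This limits the severity, but it does not make the printed figure right.

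**Silence on uptake and attrition is no error.** A reader might infer that the article conceals weak precision for these criteria. A condensed article need not give planned precision for every proportion. The figures in Step 6 are useful only as an alternative justification.

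**Recruitment capacity.** It is also tempting to infer that 600 eligible women cannot be found. The Study Setting section gives an annual figure of 700 to 1000 women, but it is not clear whether this is per clinic or for all three, and the article states no recruitment period. The inference is not supported.

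**Conclusion.** The concern holds as an error in a stated figure, of moderate severity. The ±8 points fit a denominator of about 54 to 60, whereas the design implies about 600 eligible women and about ±2.4 points, roughly a third of the stated half-width. The figure is therefore not this design's precision and gives no support to the choice of 60.

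This rests on the article's own 10% and its target of 60 randomized, and on reading the sample in that sentence as those 60 women. It does not show that 60 is the wrong number.

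The sentence also calls randomized-of-eligible the primary outcome, while Feasibility Outcomes makes the register-identified proportion primary. If the 10% refers to eligible women, the register-based denominator can be no smaller than 600, and its proportion no larger than 10%. The half-width would then be at most about 2.4 points.

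**What to change.** Replace the precision sentence and its formula with, for example:

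> With 60 women randomized and an expected 10% of eligible women randomized, about 600 eligible women form the denominator, giving a 95% CI of about ±2.4 points.

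Then make the denominator agree with Feasibility Outcomes. Either name eligible women as the primary denominator in both places, or base the sentence on register-identified women. The second choice needs an expected proportion for that group, which the article does not give separately; the calculation then follows Step 3 with that value.

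If a precision argument for 60 itself is wanted, use the proportions whose denominators the sample fixes: 20% attrition among 60 is estimated to about ±10 points, and 50% uptake among 30 to about ±18 points. Otherwise let the SD rationale stand alone.

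The cost is wording and one recalculated figure. No participants are added, and the progression criteria and analysis stay as they are. If the optional figures are quoted, they will look less favourable than the single ±8 now in print.
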